## 10. Statistics

### Statistical tests

With all the variables involved in the study, either the main variable of evaluation, and the control variables the following exploratory and diagnosis analysis will be carried out

**Exploratory analysis:**

- a) Descriptive graphs will be done, depending on the type variable. With the quantitative variables (age, weight, illness duration), box-plot graphs, frequency histogram, and confidence intervals graphs for the mean; with the qualitative variables (sex, smoking habit, reaction to medications, proportion of patient with each adverse reaction), out pie graphs and frequency histograms.
- b) With the qualitative variables correspondences factorial and cluster analysis will be carried out to study if there is some tendency of individuals grouping in determined categories of the variables and to infer their importance in the treatment response prediction.
- c) With the quantitative variables the descriptive analysis with the estimates of the central tendency and dispersion measures that satisfy the assumptions of normal distribution: mean, mode, confidence intervals for the mean, standard deviation and maximum and minimum values. In the case of the quantitative variables that does not satisfy the assumptions of normal distribution: median, mode, minimum and maximum values, quartile range and percentiles; with the qualitative variables: the frequency histogram.

**Diagnosis:**

With the quantitative variables:

- a) To study the presence of aberrant or extreme values through the following tests: t test, prove index test and 4SD test.
- b) Depending on the type of analysis that is necessary from the confirmatory point of view, the specific diagnosis techniques will be applied: dispersion graphs, residuals with and without cover graphics, residuals with suppression, Cook's residuals, diagonal of the matrix Hatt parameters (leverages, (hi)).
- c) In case of detecting some aberrant point through these techniques, the individual's form should be revised with that observation. If the possibility that is an entry error to the database is discarded, the following step consists on consulting with the investigators the possibility of exclusion the individual of the analysis, since it can cause biases in the results interpretation, due their deviation with the rest.

With the qualitative variables:

- a) To infer the presence of extreme values of the exploratory analysis carried out (cluster analysis).
- b) and c) Similar to the quantitative variables.

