## 4. General design

**Type of trial:** Open phase II-III clinical trial.

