### **5.5 Exit criteria or interruption of the treatment after inclusion**

- Voluntary abandonment of the patient.
- Appearance of any of the above-mentioned exclusion criteria.
- Patients with worsening of the liver pathology in comparison with baseline levels, according to the investigator's criteria.
- Severe adverse reactions according to WHO guidelines
- Feverish status (more than 37.8 °C) at the moment of vaccine administration or in the 24 hour before, or any suspected or confirmed infectious diseases that results in the suspension of three vaccine administrations during the course of the immunization schedule.
- Patient's death.

Patients, once included, will be considered in the analysis even if they interrupt the treatment. Therefore, no case report form will be eliminated.

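### The outlier rule in section 10 lets investigators in an open trial consider removing patients with verified data because their values deviate, in tension with the all-included rule of section 5.5

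*Protocol*

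**What the plan says.** Section 10 of the Protocol opens its statistical tests by applying exploratory and diagnostic analyses to all variables, "either the main variable of evaluation, and the control variables". Under Diagnosis, quantitative variables are checked with several outlier tests, a 4SD test among them, and with residual and leverage measures. When a point is flagged, the patient's form is reviewed. The text then continues: "If the possibility that is an entry error to the database is discarded", the next step is "consulting with the investigators the possibility of exclusion the individual of the analysis". The reason given is "since it can cause biases in the results interpretation, due their deviation with the rest".

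Qualitative variables follow the same path. Step a) is "To infer the presence of extreme values of the exploratory analysis carried out (cluster analysis)", and the remaining steps are "b) and c) Similar to the quantitative variables".

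Three other places bear on this:
- Section 5.5: "Patients, once included, will be considered in the analysis even if they interrupt the treatment". The next sentence adds that no case report form is dropped.
- Section 4 describes the trial as "Open phase II-III clinical trial".
- Section 11 (confidentiality and disclosure of results) has sponsors and investigators analyse and interpret the results together.

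**The concern.** The exclusion step begins only after an entry error has been ruled out. It therefore acts on genuine values, it concerns the whole patient rather than one data point, and its only ground is distance from the other patients. The people consulted know the treatment and may know the outcome. Nothing in the Protocol fixes a cut-off for exclusion, requires the decision to be made blind, or requires the result with all patients to be reported alongside.

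Flags need not be unrelated to outcome or arm. Initial viral load is a control variable and so is screened. Section 2.7 reports that, in the earlier study of NASVAC in patients, HBeAg-positive patients had much higher baseline loads and reached undetectability less often. Section 7 adds ALT and AST measurements after each NASVAC dose in that arm, which gives it more chances to produce an extreme value. Case-by-case exclusion under these conditions can bias both the efficacy and the safety comparison, and a reader of the report could not tell whether it had.

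**Working it through.** **Side by side.** Take one included patient with a verified but extreme value. Under section 5.5 the patient is analysed. Under section 10 the patient may be taken out after consultation. If the exclusion is made, both sections cannot be satisfied for that patient. No other place in the Protocol says which governs.

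**What the screen can reach.** Response is binary: HBV DNA undetectable at 250 copies/mL. At an assumed response proportion of 0.30, a responder lies √(0.70/0.30) = 1.53 SD from the mean and a non-responder √(0.30/0.70) = 0.65 SD. A 4SD rule cannot flag either. The routes that remain are the viral load itself (section 7 names its quantification as the main variable), baseline load, ALT and AST, residuals and leverage, and the cluster step for qualitative variables. Because the whole individual would be excluded, a flag on any of these also removes the patient from the response table.

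**Size.** The Protocol gives no figure for this point, so there is none to reproduce. Assumptions for the illustration:
- 80 per arm, from section 4 (160 patients, 80 of them on NASVAC). Number of patients in section 10 gives 60 per group.
- 30% response on interferon. The Protocol gives no rate for that arm; section 2.4 puts current treatments at around 30% on some criteria.
- Uncorrected two-sided chi-square with 1 df, at the 0.1 level stated in section 10. Sidedness is not stated there.

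Formula: z = (p1 − p2) / √[p(1 − p)(1/n1 + 1/n2)], with p the pooled proportion and χ² = z².

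*Table A, near the 0.1 level.*
- 34/80 v 24/80: 0.425 − 0.300 = 0.125; p = 58/160 = 0.3625; SE = 0.0760; z = 1.645; χ² = 2.70; p-value 0.1001.
- One NASVAC non-responder deleted, 34/79 v 24/80: 0.4304 − 0.300 = 0.1304; p = 58/159 = 0.3648; SE = 0.0764; z = 1.708; χ² = 2.92; p-value 0.088.

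*Table B, near the 20-point criterion.* Two NASVAC non-responders and two interferon responders are deleted (4 of 160, 2.5%). The one-sided test uses H0: δ ≤ 0.20, with z = (p1 − p2 − 0.20) / √[p1(1 − p1)/n1 + p2(1 − p2)/n2].

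| | 38/80 v 24/80 | 38/78 v 22/78 |
|---|---|---|
| Difference | 0.475 − 0.300 = 17.5 points | 0.487 − 0.282 = 20.5 points |
| Chi-square p, no difference | 0.023 | 0.008 |
| One-sided p, δ ≤ 0.20 | (0.175 − 0.20)/0.0758 = −0.33; 0.63 | (0.205 − 0.20)/0.0762 = 0.07; 0.47 |

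The deletions in Table B cross the observed 20-point success criterion of the interim analysis and nothing else. The chi-square is significant at 0.1 both before and after, and the δ ≤ 0.20 hypothesis is not rejected before or after.

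*Table C, 60 per arm.* 26/60 v 18/60 has p = 0.130; deleting two NASVAC non-responders (26/58) gives 0.096.

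*Table D, far from a threshold.* 30/80 v 24/80 has p = 0.316. It takes 11 deletions of NASVAC non-responders to fall below 0.10 (30/69 v 24/80, p = 0.088) and 20 to reach 20 points (30/60 v 24/80).

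**The case against.** The strongest reply is that the text only provides for consultation about a possible exclusion after a form review. A reader might infer that flagged patients are removed automatically, or that deletions would decide the trial. The documents support neither. An ordinary responder or non-responder cannot be a 4SD outlier, and deleting in opposite response directions in the two arms, as in Table B, is not a pattern that the listed tests produce by themselves. The effect shrinks quickly away from a threshold, and on the δ ≤ 0.20 hypothesis neither Table A nor Table B changes the conclusion (Table A: one-sided p 0.84 before, 0.82 after).

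A reader might also infer that section 5.5 expressly forbids outlier exclusion. It does not: the sentence closes the exit criteria, speaks of patients who interrupt treatment, and never mentions outliers. Nor does the Protocol say that an ALT flare would disappear from the safety data, since all adverse events are to be recorded and tabulated. Rank methods for non-normal ALT and AST are already planned.

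All of this stands and limits the size of the point. It does not remove it. The opening words of section 5.5 cover patients once included, and its follow-on sentence about case report forms is unqualified. The discretion over verified data is written into the Protocol, so a separate analysis plan would have to overrule the text rather than fill a gap.

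**Conclusion.** The point holds as a defect of the stated rule. Section 10 gives unblinded investigators discretion to consider excluding whole patients with verified data, on any variable including the main one, only because the values deviate. It sets no cut-off for exclusion, no blinded decision and no required all-patients result, and it is in tension with section 5.5.

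The possible effect is conditional. Near the 0.1 level, one deletion can be enough with 80 per arm and two with 60. Near 20 points, four deletions cross the interim criterion only. Far from a threshold, 11 to 20 would be needed. These sizes rest on hypothetical tables, an assumed 30% control response and a two-sided uncorrected chi-square against no difference. The conclusion itself rests on the text and does not depend on which sample size is right. It should be corrected before any outcome data are seen, because a decision on exclusions made afterwards cannot be shown to be independent of the results.

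**What to change.** Rewrite item c) of Diagnosis in section 10:
- Outlier and cluster checks serve only to find and correct data errors.
- Every included patient with verified data stays in all efficacy and safety analyses, with a cross-reference to section 5.5.
- An analysis without influential points may be shown only as a labelled sensitivity analysis, beside the all-patients result.
- The exclusion step for qualitative variables is deleted.

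Add to section 5.5 that the rule covers extreme values as well as interrupted treatment. For ALT and AST as quantitative variables, rely on the rank methods already named in section 10 under biochemical status and adverse events. The binary HBV DNA endpoint needs no transformation.

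The cost is wording only: no extra patients, visits or tests.

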## Evaluation of the viral infection markers and statistic hypothesis

**HBV-DNA:** Response: Undetectability of HBV DNA in the serum of infected patient by using a quantitative PCR assay with 250 copies/mL as a viral detection limit of sensitivity at the end of therapy with NASVAC TVC as well as in every study cut starting from dose number five and ending at one year after treatment started.

The success criteria will be assessed one year after study started however it can be evaluated for Interim Analysis according to the date of virological assessment.

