### **3. Ethics and Medical Deontology**

#### **General ethical considerations**

The trial is justified from the ethical point of view because:

- The study is carried out according to the principles of the Declaration of Helsinki on investigations with human beings for therapeutics purposes. The patients will receive the medical care and the normal general treatment that is applied in these cases.
- CHB is a slow developing disease. The fact of being 6 – 12 months without any of the specific recognized treatments will not affect significantly the patients' evolution. Besides, follow-up will be very cautious and upon any sign of disease progression, the patient will be withdrawn from the study treatment and given a recognized specific anti-hepatitis therapy (interferon alpha or Lamivudine). In all cases patients included in the trial, after its completion will receive one of these treatments, if the principal patient and investigator decide.

- It is possible that the patients obtain benefit from their participation in the study since there are reasonable evidences that vaccination can improve their condition according to phase I results.
- Treatment of CHB patients with NASVAC, according to the results obtained at CIGB, does not represent additional risk for the patients. It is a quite safe intervention, with a very low probability of associated adverse reactions. Doctors can properly treat the possible adverse reactions and a favorable risk-benefit balance justifies them.
- Written consent of individuals will be requested, after properly informing about the objectives of the investigation, treatment to be subjected and possibility to refuse to participate in the trial at any moment without consequences to his medical care. When publishing, the confidentiality of the individuals' personal data will be guaranteed.
- All patients unable to satisfactorily control the viral load will be treated with available antiviral drugs, according to their physician decision, independently whether they belong to the control or treatment groups.
- There are preliminary evidences of safety and efficacy after the first clinical trial using NASVAC in chronic hepatitis B patients, conducted in Dhaka, Bangladesh, as previously described in the present protocol.

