### **Statistical hypothesis**

It is expected that the administration of NASVAC TVC, as defined in the present protocol, to chronic hepatitis B patients, will improve the specific anti-HBV immune response of treated patients and consequently will significantly increase the percentage of patients reducing the viral load to undetectable levels after treatment completion compared to the group administered with Pegylated Interferon, expecting a difference between groups of more than 20%.

H0: Equivalency in the percentage of chronic hepatitis B patients reducing the viral load to undetectable levels. Formally,  $H_0: \delta \leq \delta_0 = 0.20$  where  $\delta$  represents the difference between viral seronegativization, based in quantitative PCR assay with a sensitivity of 250 copies/mL, in the group treated with NASVAC compared to the group treated with Interferon.

H1: Superiority in the percentage of chronic hepatitis B patients reducing the viral load to undetectable levels. Formally,  $H_1: \delta > \delta_0 = 0.20$  where  $\delta$  represents the difference between viral seronegativization, based in quantitative PCR assay with a sensitivity of 250 copies/mL, in the group treated with NASVAC compared to the group treated with Interferon.

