## **Evaluation of the biochemical status**

### **Transaminases: Response**

#### **ALT / AST:**

**Sustained normalization** (reduction to values under 40 IU during a period of three months time) in at least 20% compared to the initial number of patients with altered (more than 40 IU) at the beginning of treatment.

**Normalization:** Reduction to values under 40 IU after one year.

It will be studied for Interim analysis different periods of time and compared to baseline level as described in Interim analysis: after five dosis, after ten dosis, after 24 weeks (6 months) or after 56 weeks (one year)..

The ALT and AST values in serum will be compared between groups and within each group, as quantitative variables, by Student's t or the Mann-Whitney's U test, depending on the normality or not of their distributions. Paired analysis will be also performed within each group to know whether a significant change has occurred in these patients.

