### **Interim analysis**

After 5 and 10 administrations and also at 48 weeks, patients will be tested by PCR to quantify HBV DNA in serum as well as for HBsAg and HBeAg seroconversion. A comparative study will be conducted for the same variables for internal comparisons between both groups in order to have a reference to standard treatment with a recognized efficacy.

a) A 20% superior percentage of viral load reduction to undetectable levels in the group treated with NASVAC compared to PegIFN treated group in any of the virological study cuts will be considered as a success criteria for the Interim Analysis.

b) A superior difference in the proportion of patients with ALT normalization or combined ALT normalization and viral load reduction to undetectable levels at a defined time (5, 10 dosis or 48 weeks) between groups will be considered a success criteria for the Interim Analysis.

e) A sustained biochemical (ALT) response during three consecutive determinations after dose number 10 will be considered a success criteria.

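### The week of the primary HBV DNA response is not fixed, and since NASVAC ends at week 24 and interferon at week 48, the choice decides what is compared

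*Protocol*

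**What the plan says.** The main efficacy variable is serum HBV DNA, and response is undetectability on a PCR with a limit of 250 copies/mL. The protocol times that response in several ways.

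- **Statistical hypothesis (section 10; section 2 has the same timing):** the tested percentage is of patients "reducing the viral load to undetectable levels after treatment completion compared to the group administered with Pegylated Interferon".
- **Evaluation of the viral infection markers (section 10), first sentence:** response is read "at the end of therapy with NASVAC TVC as well as in every study cut starting from dose number five and ending at one year", the year being counted from the start of treatment.
- **Same paragraph, second sentence:** "The success criteria will be assessed one year after study started however it can be evaluated for Interim Analysis". Here the year is counted from the start of the study.
- **Interim analysis (section 10):** cuts fall after 5 doses, after 10 doses and at 48 weeks. A 20% advantage "in any of the virological study cuts will be considered as a success criteria for the Interim Analysis".
- **ALT / AST (section 10):** the periods include "after 24 weeks (6 months) or after 56 weeks (one year".

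The visit table in section 7 has baseline and weeks 12, 24, 36, 48, 72 and 96. It labels week 24 as end of treatment for the vaccine and week 48 as end of treatment for interferon. Section 12 supplies interferon for 48 weeks, and section 4 stops NASVAC after both cycles.

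On other antivirals, section 3 (General ethical considerations) states "All patients unable to satisfactorily control the viral load will be treated with available antiviral drugs", in either group and with no time given. Section 5.5 keeps every included patient in the analysis, even after treatment is interrupted. The concomitant-treatment rules in section 6 say specific anti-hepatitis drugs should be avoided.

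**The concern.** The two treatments have different lengths, so the week of assessment determines which question the trial answers. An early reading sets a finished course against an unfinished one. A week-48 reading sets sustained response after stopping against response at the end of treatment. The alternative hypothesis requires a difference above 0.20, and a change of that order could come from the choice of week alone. With several weeks available in the text, the choice could be made, or disputed, after the data are seen.

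A second, smaller point concerns attribution. Response is defined by the PCR result alone. A patient who becomes undetectable on another anti-HBV drug meets that definition unless a further rule says otherwise.

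**Working it through.** **1. Time off treatment at each candidate week.** Inputs from the visit table: end of NASVAC at week 24, end of interferon at week 48. Weeks off treatment = assessment week − end-of-treatment week.

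| Assessment week | NASVAC, weeks off | Interferon, weeks off | In the visit table? |
|---|---|---|---|
| 24 | 24 − 24 = 0 | still on treatment, 24 of 48 weeks given | yes |
| 48 | 48 − 24 = 24 | 48 − 48 = 0 | yes |
| 52 | 52 − 24 = 28 | 52 − 48 = 4 | no |
| 56 | 56 − 24 = 32 | 56 − 48 = 8 | no |
| 72 | 72 − 24 = 48 | 72 − 48 = 24 | yes |

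Check on the week-24 label: ten doses every 14 days put dose ten at 9 × 14 = 126 days, or week 18, if there is no gap between cycles. Counted from that dose, NASVAC is 48 − 18 = 30 weeks off at week 48. The labelled figure of 24 weeks is the smaller of the two.

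**2. Matching the arms.** Equal time off treatment (24 weeks) pairs NASVAC at week 48 with interferon at week 72. Both visits exist.

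**3. What one year means.** The interim section lists 48 weeks as an interim cut, the transaminase section equates one year with 56 weeks, and no visit lies between weeks 48 and 72. The one-year assessment is therefore either the week-48 visit or a visit that is not scheduled.

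**4. How much the week can matter (assumed rates).** Take NASVAC at 50% at week 48; the protocol's section on clinical experience reports 50% undetectable at 12 months in the earlier patient study. Assume interferon is also 50% at end of treatment, and that 20 to 60% of its responders relapse by week 72.

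- Difference at week 48: 50 − 50 = 0 points.
- Interferon at week 72: 50 × (1 − 0.20) = 40%, down to 50 × (1 − 0.60) = 20%.
- Difference at 24 weeks off in each arm: 50 − 40 = 10 points, up to 50 − 20 = 30 points.

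With interferon at 40% at end of treatment, the difference is 10 points at week 48 and 18 to 34 matched. With interferon at 60%, it is −10 at week 48 and 2 to 26 matched.

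**5. Patients given another antiviral (assumed rates).** Apparent rate = p + (1 − p) × f × s, where p is the true response, f the fraction of non-responders given another drug, and s the fraction of those suppressed.

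- Both arms truly 30%, f = 10 to 30% in NASVAC only, s = 50 to 80%: spurious difference from 0.70 × 0.10 × 0.50 = 3.5 points to 0.70 × 0.30 × 0.80 = 16.8 points in favour of NASVAC.
- Both arms truly 30%, f = 20% in each: 0 points.
- True rates 50% and 30%, f = 20% in each: with s = 50%, 55 − 37 = 18 points; with s = 80%, 58 − 41.2 = 16.8 points. The true 20 points shrinks.

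The documents give no value for f or s, so neither size nor direction can be fixed.

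**6. HBV DNA tests budgeted.** Section 12 lists four per patient. Baseline plus the three interim cuts is 1 + 3 = 4, so a week-72 test may not be provided for. The cells of the visit table are not visible, so this is an inference only.

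**The case against.** The paragraph on viral markers can be read as selecting one year for success and leaving the other cuts to interim analysis. By one year both arms have finished, so the hypothesis wording is compatible with it. The rule accepting any cut is expressly an interim rule, and the 56 weeks belongs to ALT and AST, not to HBV DNA. The two starting points for the year may well be meant as the same day. That reading is reasonable, but it still leaves one year without a week, and the first sentence of the same paragraph places the end of NASVAC therapy and every cut on the same footing.

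A common time from start is also a legitimate comparison of two strategies of different length. That stands. A reader might infer that a week-48 comparison is invalid or tilted towards the vaccine; the documents support neither. If interferon responders relapse, week 48 works against NASVAC. Interferon is at end of treatment only if one year means week 48; at weeks 52 or 56 it would be 4 or 8 weeks off.

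A reader might further infer that rescued patients are scored as responders. No section says so. It follows only from combining the PCR definition, the retention of all patients and the permitted antivirals. The ethics statement may partly concern care after the trial, although the same section also allows another therapy on progression during the study. An analysis plan not shown here may settle the scoring. An inflation calculated from rescue in the NASVAC arm alone would not be supported either, because the provision covers both arms.

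**Conclusion.** The inconsistency holds. The primary response is timed differently in the hypothesis, the response definition and the interim rule, and one year is tied to no scheduled week. The consequence is concrete: 24 of 48 weeks of interferon given at week 24, and 24 weeks against 0 weeks off treatment at week 48. Those figures rest on the visit table's end-of-treatment labels. Under the relapse rates assumed above, the estimated difference moves by 10 to 30 points between the week-48 and the matched reading when both arms stand at 50% at week 48, which is comparable with the 20-point margin. The actual relapse rate is not in the documents.

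The point on other anti-HBV drugs is secondary: the definition as written does not exclude such patients, and the size and direction of any bias are unknown. The remedy is a clarification that should be made before any comparative analysis.

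**What to change.** 1. Name one primary time, week 48 from the start of treatment in both arms, in both statements of the hypothesis, in the response definition and in the interim section. Possible wording: *primary response is HBV DNA undetectable by the 250 copies/mL PCR at week 48, counted from the patient's first dose of assigned treatment, in both groups.* Remove week 48 from the list of interim cuts and align the 56 weeks in the transaminase section with it.
2. Make the cuts after 5 and 10 doses, where interferon is unfinished, descriptive and not grounds for declaring success.
3. State that week 48 compares NASVAC 24 weeks off treatment with interferon at end of treatment. Base any durability claim on 24 weeks after end of treatment in each arm: NASVAC at week 48, interferon at week 72.
4. Add to the analysis definition that a patient who starts another anti-HBV drug counts as a non-responder from that date. The statements on other antivirals in General ethical considerations and in the concomitant-treatment rules must be reconciled; which clinical rule applies is for the sponsor and investigators.

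Cost: wording, one more table and, if HBV DNA is not already measured at week 72, one PCR at an existing visit. Response rates may fall slightly in either arm under item 4.
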